#### Secondary outcomes

2.5.2

1.Daily Stool Record (DSR)
a.**Timeframe**: Pre-FMT, during FMT, and at 1, 2, 3, 4, 5, 6 weeks, 3 months, 6 months, 9 months and 12 months post-FMT.b.**Description**: Daily documentation of stool characteristics using the Bristol Stool Scale. The percentage of days with abnormal bowel movements (e.g., abnormal consistency, absence of stool, or use of GI medications) is calculated, with higher percentages indicating worse symptoms.2.Social Responsiveness Scale (SRS)
a.**Timeframe**: Pre-FMT, 3 months, 6 months,9 months and 12 months post-FMT.b.**Description**: A 65-item questionnaire assessing social skills. Items are scored 0 (“never true”) to 3 (“almost always true”), with total scores ranging from 0 to 195. Higher scores indicate greater social impairment.3.Aberrant Behavior Checklist (ABC)
a.**Timeframe**: Pre-FMT, 3 months, 6 months,9 months and 12 months post-FMT.b.**Description**: A 58-item checklist evaluating maladaptive behaviors. Total scores range from 0 to 174, with ≥31 indicating autism tendency and >53 confirming an autism diagnosis. Higher scores reflect more severe behavioral issues.4.Microbiota Analysis
a.**Sequencing Method:** Fecal samples will be subjected to metagenomic next-generation sequencing (mNGS) to comprehensively characterize the gut microbiota at both taxonomic and functional levels. Total microbial DNA will be extracted from fecal samples, followed by library construction and shotgun sequencing on an Illumina NovaSeq platform (or equivalent), aiming for a sequencing depth of at least 10 Gbp per sample to ensure adequate coverage for both abundant and rare species, as well as functional gene analysis.b.Bioinformatic and Statistical Analysis Pipeline:

The raw sequencing data and subsequent analyses will adhere to the following rigorous bioinformatics procedure to ensure accuracy and reproducibility.

Step 1: Raw Data Quality Control.

To assess sequencing quality and detect potential contamination, FastQC (Version 0.12.1) (36) and MultiQC (Version 1.15) (37) will be utilized with default parameters. Key quality metrics include ≥80% of bases with a Q-score >30, adapter content <5%, and GC distribution within the expected range of 40%–50%. The output report, ASD_FMT_Raw_QC.html, will be reviewed to exclude samples that fail to meet these criteria.

Step 2: Read Trimming and Host DNA Removal.

In this step, KneadData (Version 0.12.0) (38) will be used to perform read trimming and host DNA removal. Using the GRCh38.p14 human reference genome, KneadData will first trim the reads to remove low-quality bases and adapters, then filter out any reads mapping to the human genome. This will ensure that host-derived contamination is minimized to ≤5%. After the filtering process, the remaining high-quality clean reads are expected to constitute at least 70% of the original raw reads, providing an enriched dataset of non-host sequences for subsequent analyses.

STEP 3: Taxonomic Profiling.

After obtaining the high-quality clean reads, high-specificity taxonomic profiling will be performed to classify the microbial community at the species level. This will be achieved using MetaPhlAn4 (Version 4.1.1) (39) and the database mpa_vJun23_CHOCOPhlAnSGB_202403, which maps the sequencing reads to a set of species-specific marker genes. Beside the default parameters, the option “-s” will be added in the parameter so as to generate SAM files for raw sequence alignment output. The result will be a detailed table showing the relative abundance of each species present in the samples, enabling precise classification and valuable insights into the microbial community composition of the samples.

STEP 4: Functional Profiling.

Following taxonomic profiling, functional profiling will be performed to assess the functional capabilities of the microbial communities. This will be conducted using HUMAnN3 (Version 3.8) (40), which maps the high-quality, host-depleted reads to known gene families and metabolic pathways, offering a detailed functional profile of the microbial communities. The output will include a table of relative abundances of predicted pathways and gene families, with particular attention to those pathways that may be relevant to the effects of FMT. This will help identify functional shifts in microbial communities post-FMT, offering insights into the metabolic mechanisms potentially linked to improvements in ASD symptoms.

STEP 5: *de novo* Assembly and MAG Reconstruction.

For *de novo* assembly of the metagenomic data, Megahit (Version 1.2.9) (41) will be used. This step involves assembling the high-quality, host-depleted reads into longer contiguous sequences (contigs) for further analyses. The assembly will be performed with the following parameters: –k-list 21,29,39,59,79,99,119,141\–min-contig-len 1,000\–presets meta-large\–memory 0.95\–cpu-only. After that, metagenomic binning and bin refinement will be conducted using MetaWRAP (42).The MetaWRAP refinement aims to enhance the quality of our MAG (metagenome-assembled genomes) binning, utilizing the parameters -c 50 -x 10, which retains only bins with completeness greater than 50% and contamination less than 10%. Redundancies in the MAGs will be removed with dRep Version 2.6.2 (43). MAGs will be annotated using GTDBtk Version 2.3.2 (44), and their quality will be evaluated using CheckM Version 1.0.7 (45). Gene prediction will be performed using Prodigal Version 2.6.3 (46), clustering of genes with CD-HIT Version 4.8.1 (47).

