#### Secondary objectives

2.1.2

2.1.2.1 To analyze changes in gut microbiota composition during FMT treatment in children with ASD.

2.1.2.2 To explore correlations between core microbiota and clinical outcomes.

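### The raw-read GC window of 40% to 50% excludes samples partly on the microbial composition that the trial sets out to measure

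*Protocol article*

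**What the plan says.** Section 2.5.2 of the protocol article, item 4 (Microbiota Analysis), sets out the sequencing pipeline. The first stage is headed "Step 1: Raw Data Quality Control" and has a stated aim: "To assess sequencing quality and detect potential contamination". It gives three limits. Two concern the library and the run: "Key quality metrics include ≥80% of bases with a Q-score >30, adapter content <5" (per cent). The third is "GC distribution within the expected range of 40%–50" (per cent). The consequence of failing is also stated: the report "will be reviewed to exclude samples that fail to meet these criteria".

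Trimming and host removal come only in Step 2, where "KneadData will first trim the reads to remove low-quality bases and adapters, then filter out any reads mapping to the human genome".

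Section 2.1.2 gives as a secondary objective "To analyze changes in gut microbiota composition during FMT treatment in children with ASD". Section 2.7.2 plans diversity comparisons across time points, differential abundance, paired tests, and associations of microbial features with CARS, ABC, SRS and GSRS. The hypothesis at the end of the Introduction links clinical improvement to restored microbial diversity and function.

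**The concern.** A quality filter should remove samples for technical failure. GC content is not purely technical in a metagenomic sample, because it also reflects which organisms are present and in what proportions. A sample can therefore fall outside the window because the child's flora is unusual at baseline, or because FMT has changed it markedly, with nothing wrong in the laboratory.

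If so, inclusion in the analysis depends on the outcome, possibly to a different degree at different visits. The estimates at stake are the changes in diversity and abundance from baseline and the correlations with symptom scores. In a single-arm trial of 30 children, the within-child comparison with baseline is the main microbiota contrast, so a lost baseline sample is costly.

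**Working it through.** The plan gives no figure for GC failures, so there is none to reproduce. The check has three parts.

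**1. Does GC depend on composition?** Yes, by identity:

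sample GC = Σ (read share of genome × GC of genome).

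Let the rest of the community have mean GC *m* and one taxon have GC *g*. The read share at which the sample mean leaves the window is

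- upper limit: (50 − *m*)/(*g* − *m*)
- lower limit: (*m* − 40)/(*m* − *g*)

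The document gives no genome GC values. The values of *m* and *g* below are assumptions, shown as a range.

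| *m* | *g* | Limit crossed | Share needed |
|---|---|---|---|
| 42 | 55 | 50% | 8/13 = 62% |
| 44 | 60 | 50% | 6/16 = 37.5% |
| 46 | 60 | 50% | 4/14 = 28.6% |
| 48 | 60 | 50% | 2/12 = 16.7% |
| 48 | 65 | 50% | 2/17 = 12% |
| 42 | 28 | 40% | 2/14 = 14% |
| 48 | 36 | 40% | 8/12 = 67% |

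For *m* of 42–48, the upper limit needs a share of 12% to 62% (*g* of 55–65) and the lower limit 14% to 67% (*g* of 28–36).

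**2. What would such a cut do to an estimate?** As an illustration only, let the taxon (*g* = 60) have a true mean share of 20% across samples, with shares following a Beta(1.6, 6.4) distribution.

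| *m* | Samples excluded | Mean share in those kept |
|---|---|---|
| 44 | 11% | 16.6% |
| 46 | 24% | 14.0% |
| 48 | 52% | 9.1% |

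Here the taxon's abundance is understated. The direction is not general. A sample dominated by one extreme-GC organism also has low diversity. Dropping such samples at follow-up would make a diversity gain look larger, and dropping them at baseline would make it look smaller.

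**3. What does an exclusion cost in pairs?** Table 1 has nine recipient stool windows: baseline, the FMT period, 1, 2 and 4 weeks, and 3, 6, 9 and 12 months. At one sample per window that is 30 × 9 = 270 samples. Losing one baseline sample removes that child's 8 contrasts with baseline. The other 8 samples can still be compared with each other.

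If each sample failed independently with probability 5% or 10% (assumed), the expected number of complete baseline/follow-up pairs would be 30 × 0.95² = 27.1 or 30 × 0.90² = 24.3.

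**The case against.** The strongest reply is that the size is all assumption. The document gives no genome GC, no typical sample GC and no failure rate. It calls the window an expected range and ties Step 1 to quality and contamination. On the assumed values a single taxon may need well over a third of all reads to push a sample out, and nothing in the document shows that FMT produces such a shift. This stands, and it limits the finding to a possible bias of unknown size.

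It can also be said that a review of the report leaves room for judgement, and that re-sequencing and sensitivity runs may be set out in a fuller document. The point does not rest on their absence. It rests on a stated rule whose stated consequence is exclusion.

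A reader might infer more than the text supports:

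- **That the rule cannot be met**, because individual reads scatter beyond 40–50% by chance. That requires every read to lie in the window. The text sets a per-sample metric judged from a report, and mean GC is the natural reading.
- **That host DNA pushes samples out of the window.** The rule does precede host removal, but the document gives no host GC value from which this could be shown.
- **That the adapter and Q30 limits also select on composition.** They measure library and run quality, which is Step 1's stated aim. Moving them to after trimming is a preference, and they would then say little about the library.
- **That a lost baseline ends all of a child's comparisons.** Only the 8 contrasts that use baseline go, and section 2.7.2 also lists analyses that are not paired tests.

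**Conclusion.** The point holds in a limited form. The protocol states that samples whose raw-read GC lies outside 40–50% are to be excluded, and sample GC depends partly on the organisms present. The rule can therefore remove samples because of the composition, or the change in composition, that the trial wants to estimate. An unusual GC value is a reason to look for contamination and is not proof of it.

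The number of samples affected and the direction of any bias cannot be known from the document. The mechanism needs only the mixture identity. The percentages in the illustration rest on assumed GC values and an assumed spread of shares. The effect is confined to the microbiota outcome and its associations with clinical scores. The analyses of GSRS and CARS change, safety and sample size are not affected. It is worth correcting mainly because the correction is cheap.

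**What to change.** In section 2.5.2, Step 1:

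1. Remove the GC range as an automatic exclusion criterion and keep it as a flag that triggers a contamination check.
2. Exclude a sample only for demonstrated contamination or for too few clean non-host reads after Step 2. Fix that yield limit in advance; the section already states an expected share of clean reads (70% of raw) and a depth target (10 Gbp).
3. Have the decision made without knowledge of visit or clinical outcome.
4. Report the microbiota results with and without the flagged samples, and list flagged and excluded samples by visit.

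The Q30 and adapter limits may stay on raw reads as library-quality checks. As an option, a sample that fails only on adapter content could be judged on its clean read yield after Step 2 before it is discarded.

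The cost is a wording change and one added sensitivity run, with no new samples or sequencing. The small downside is that a few borderline samples stay in the main analysis.

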### Safety assessment

2.6

Safety monitoring will include documentation of adverse events (AEs), serious adverse events (SAEs), and abnormal laboratory parameters throughout the study, extending to the 12-month final follow-up.
1.Definitions and Grading: AEs will be defined as any untoward medical occurrence in a participant, regardless of its suspected relationship to the intervention. SAEs will be defined as any AE that results in death, is life-threatening, requires inpatient hospitalization, or results in persistent disability. All AEs will be graded for severity using the Common Terminology Criteria for Adverse Events (CTCAE v5.0, 2018).2.Causality Assessment: The Principal Investigator (PI) will assess all AEs for their potential relationship to the FMT intervention (classified as unrelated, unlikely, possible, probable, or definitely related).3.SAE Reporting: All SAEs will be reported by the study team to the PI within 24 h of awareness. The PI will then report the SAE to the Shenzhen Children's Hospital Ethics Committee (EC) within 7 days.4.Long-Term Safety Monitoring: (New section for comment 6) In addition to routine AE/SAE reporting, the extended 12-month follow-up will specifically monitor for potential long-term risks. This monitoring will include:
a.Neurodevelopmental Parameters: Assessment for any new onset or significant worsening of neurological or psychiatric symptoms using the standardized scales (CARS, SRS, ABC) and clinical evaluation.b.Immune and Inflammatory Parameters: Monitoring for new onset of allergic, atopic, or autoimmune symptoms. Laboratory tests at 6 and 12 months will include Complete Blood Count (CBC) with differential, high-sensitivity C-reactive protein (hs-CRP), and Erythrocyte Sedimentation Rate (ESR).c.Metabolic Parameters: Laboratory tests at 6 and 12 months will include Fasting Blood Glucose, Glycated Hemoglobin (HbA1c), a Fasting Lipid Profile, a Liver Function Panel (e.g., ALT, AST, ALP, Total Bilirubin), and a Renal Function Panel (e.g., BUN, Creatinine) to monitor for metabolic disturbances.d.GI Status: Continued monitoring of GI symptoms via GSRS and DSR.5.Data and Safety Monitoring Board (DSMB): Given the interventional nature of the study and the vulnerable pediatric population, an independent DSMB will be established. The DSMB will be composed of at least three independent experts (e.g., a pediatric gastroenterologist, a child psychiatrist, and a biostatistician) not affiliated with the study. The DSMB will convene to review cumulative safety data after the first 10 participants have completed the 6-week follow-up, and thereafter as needed, to protect participant safety and ensure study integrity.

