#### Primary objective

2.1.1

To investigate the clinical efficacy and safety of FMT in children with ASD.

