##### Nasojejunal tube placement, sedation, and risk management

2.4.4.2

Administration of FMT via the upper GI tract carries specific procedural considerations and risks that must be carefully managed in a pediatric population.
Procedure: The nasojejunal tube will be placed by an experienced pediatric gastroenterologist under the direct visualization of a video endoscope, confirming that the distal tip is correctly positioned in the jejunum past the ligament of Treitz.Sedation: Recognizing that NJ tube placement can cause significant discomfort, anxiety, and requires patient cooperation, the procedure will be performed with appropriate sedation. Each child will undergo a pre-procedural assessment by a pediatric anesthesiologist to determine the optimal, individualized sedation plan. This plan may range from moderate (“conscious”) sedation to general anesthesia, depending on the child's age, anxiety level, and clinical condition, in accordance with the American Academy of Pediatrics guidelines for procedural sedation.Risk Disclosure and Management: The informed consent process will explicitly detail the specific risks associated with upper GI tract administration and NJ tube placement. These risks include, but are not limited to: discomfort or pain during tube placement, risk of aspiration of gastric or fecal contents, potential for mucosal injury or nosebleed, tube dislodgement (e.g., due to coughing or vomiting), and the risks inherent to the sedation or anesthesia itself. Patients will be monitored closely by trained clinical staff during and after the procedure for any adverse events.

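### The SAE definition is a closed list without prolonged hospitalisation or medically important events, so some procedural harms would miss the SAE count and expedited reporting

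*Protocol article*

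**What the plan says.** Section 2.6 (Safety assessment), item 1, defines adverse events broadly: "AEs will be defined as any untoward medical occurrence in a participant, regardless of its suspected relationship to the intervention". It then defines serious events narrowly: "SAEs will be defined as any AE that results in death, is life-threatening, requires inpatient hospitalization, or results in persistent disability". The second sentence has no opening such as *including* or *for example*, and no other section adds a criterion.

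Two sets of rules follow from these definitions.

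- **All AEs.** The scope is wide: "Safety monitoring will include documentation of adverse events (AEs), serious adverse events (SAEs), and abnormal laboratory parameters throughout the study", to the 12-month visit. Every AE is graded by CTCAE v5.0, and the principal investigator "will assess all AEs for their potential relationship to the FMT intervention".
- **SAEs only.** Item 3 sets the clock: "All SAEs will be reported by the study team to the PI within 24 h of awareness". The principal investigator then has 7 days to inform the Ethics Committee.

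Section 2.4.4.2 lists the procedural harms expected from nasojejunal delivery, among them "risk of aspiration of gastric or fecal contents, potential for mucosal injury or nosebleed, tube dislodgement", together with the risks of sedation or anaesthesia. Section 2.4.4.3 schedules infusions on Days 1, 3 and 5. The primary objective in section 2.1.1 is "To investigate the clinical efficacy and safety of FMT in children with ASD".

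**The concern.** Two common routes to seriousness are missing. An event in a child who is already admitted does not, read literally, require hospitalisation; it prolongs it. An event treated promptly, so that no listed outcome occurs and no admission follows, also meets none of the four criteria even if it was clinically important.

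The harms foreseen in section 2.4.4.2 occur around supervised procedures, where staff are on hand to treat them, so both routes are plausible in this trial. What is at stake is the label and what depends on it: the SAE count that will be reported for a trial with safety in its primary objective, and the only reports in the document that carry a deadline.

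**Working it through.** The point concerns a definition, so the main check is to hold the foreseen harms against the printed criteria. The plan gives no figure for SAEs that could be reproduced.

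**Step 1. Criteria.** Section 2.6, item 1 gives four: death; life-threatening; requires inpatient hospitalisation; persistent disability.

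**Step 2. Harms from section 2.4.4.2 against the four criteria.**

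| Event | Criterion met | Result |
|---|---|---|
| Airway or anaesthetic event that threatens life | Life-threatening | SAE |
| Non-life-threatening aspiration in a day patient, who is then admitted | Hospitalisation | SAE |
| Non-life-threatening aspiration in a child already admitted, stay lengthened | None | AE only |
| Mucosal injury treated without admission, no lasting disability | None | AE only |

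The documents do not say whether children are inpatients during Days 1 to 5. The gap does not depend on this. If they are inpatients, the third row applies. If they are day patients, the fourth row applies, so at least one gap is open in either case.

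**Step 3. What the label controls.**

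- Not dependent on it: documentation, CTCAE grading, causality assessment, and inclusion in the cumulative safety data that the DSMB reviews (section 2.6, items 1, 2 and 5).
- Dependent on it: the SAE count, the 24 h report and the 7-day report (item 3). No section ties a CTCAE grade or a causality class to a deadline.

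**Step 4. Timing.** The first scheduled DSMB review follows completion of the 6-week visit by the first 10 participants. If every child receives all three infusions:

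- infusions in those children: 10 × 3 = 30;
- infusions in the whole trial: 30 × 3 = 90;
- share given before the first scheduled review: at least 30/90 = one third, plus any in children enrolled meanwhile.

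Over that period SAE reporting is the only notification with a deadline.

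**Step 5. Illustration of what one event does to the reported proportion.** Event counts are assumed; n = 30 is from section 2.8. Exact (Clopper-Pearson) 95% limits are used. For zero events the upper limit is 1 − 0.025^(1/30) = 11.6%.

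| SAEs | Proportion | 95% interval |
|---|---|---|
| 0/30 | 0% | 0 to 11.6% |
| 1/30 | 3.3% | 0.1 to 17.2% |
| 2/30 | 6.7% | 0.8 to 22.1% |

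With 30 children, one or two events classified differently change the SAE line visibly. The same events would still stand in the AE tables with their grade.

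**The case against.** The strongest case against the point is that nothing is lost. All AEs are documented, graded and attributed, trained staff watch for them during and after the procedure, and the DSMB sees cumulative safety data, not SAEs alone. The primary outcomes are GSRS and CARS. There is no SAE-rate endpoint and no SAE-based stopping rule, so only a descriptive count changes. Much of this stands, and it rules out two stronger readings.

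- A reader might infer that such harms would not count towards the primary safety objective. The documents do not support this: section 2.1.1 does not limit safety to SAEs, and section 2.6 keeps every AE within safety monitoring.
- A reader might want to say what share of serious procedural events would be missed. The documents give no event rate and no basis for a share, so any such figure would only restate an assumption.

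It is also fair that the most severe airway or anaesthetic events may already qualify as life-threatening, and that the prolongation route applies only if children are admitted, which is not stated.

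A last argument is that an article may shorten a definition that is complete in the full protocol or on the SAE form. This carries less weight. The article does not leave the definition out; it states one, in closed form. What remains is that, as written, some events lose the SAE label and with it the only reporting deadlines.

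**Conclusion.** The point holds in a limited form. The printed SAE definition is incomplete. Followed literally, it would classify some non-life-threatening procedural harms as non-serious: those that only prolong a stay, and medically important ones treated without admission. They would then be absent from the SAE count and from the 24 h and 7-day reports, while remaining in the AE record.

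The number of such events cannot be estimated from the documents. The consequence is for safety oversight and for a descriptive count in 30 children; no sample size, power or planned test is affected. The conclusion assumes that the definition is applied as printed and that the SAE form adds nothing to it. It does not depend on whether the children are inpatients. The Discussion relies on rigorous safety oversight to offset the limits of an open-label, single-arm design, so the definition deserves correction even though the events would not be lost.

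**What to change.** In section 2.6, item 1:

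- extend the hospitalisation criterion to *requires inpatient hospitalization or prolongs existing hospitalization*;
- add *or is an important medical event that may need intervention to prevent one of these outcomes*;
- if children are admitted for FMT, state that the planned stay is not itself an SAE.

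Make the same change on the SAE form. The cost is a sentence or two and slightly more expedited reports for the principal investigator and the Ethics Committee. No treatment rule, visit or analysis changes.
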